**Methods:**

This longitudinal study will use a cluster randomized trial design. Three high schools from six randomly selected Canadian school boards will participate and be randomized to three study arms: (1) You-CAN led by school staff; (2) You-CAN led by school staff and research team; and (3) untreated comparison group. Intervention arms 1 and 2 will deliver the You-CAN program and create a Concussion Council at their school. The Concussion Council will deliver a concussion awareness campaign and participate in an online showcase with other participating schools. In addition, arm 2 will have monthly video-calls with the research team. A survey based on the Theory of Planned Behaviour will be administered school-wide with all arms (1, 2, 3) at two time points (beginning {T_0_} and end {T_1_} of the school year). Exit interviews will be completed with the Concussion Councils and participating school staff.

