## Methods/design

### Study design

This longitudinal study uses a cluster randomized trial design with two intervention groups and an untreated comparison group (Fig. 2). This study has been approved by the Holland Bloorview Research Ethics Board (#18–826).

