### Sample size

A sample size calculation was completed based on pilot administration of this study’s main outcome measure, the Concussion Reporting and Social Support Measure (CRSS-M) (see Outcome Measures section below). The sample size was calculated using an effect size of 0.20 (α = 0.05 and power = 0.80). This is in line with previously estimated effect sizes for school-based interventions conducted with high school aged youth [26–28]. As the CRSS-M is being administered in the school-setting with support from participating school boards, principals and school staff, we expect a low attrition rate (about 10%) from the beginning {T_0_} to end {T_1_} of the school year. Based on this information, we require 140 participants to complete the survey at each participating high school.

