#### School recruitment

After obtaining approval at the school board level, three schools within each board will be invited to participate. Schools will be included in the randomization process if they are: (1) primarily English-speaking, (2) co-ed, and (3) enrol students in grades 9–12. They will be excluded if they: (1) have less than 100 students, (2) only teach distance education, or (3) are an alternative school setting. The randomization assignment will be completed using R software [29]. All school principals from the randomly selected schools will be contacted through email and telephone via publicly available contact information in order to confirm participation and provide consent on behalf of the school. Schools will be further excluded if (1) they already have an established concussion club or (2) no other size-matched schools chose to participate.

Selected schools will be matched for school size prior to the random allocation to the study arms. School size is shown to be associated with school connectedness, students’ beliefs that teachers within the school care about them as individuals, and care about their learning [30, 31]. The following categories will be used to capture school size: (1) large population size (1000+ students), (2) medium population size (400–1000 students), and (3) low population size (less than 400 students). If three schools of matched size are not interested in participating, a different size category will be selected and invited to participate. If no size-matched schools agree to participate, then the school board will be excluded from the study and a new school board will be randomly selected to participate.

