#### Intervention assignment

Once consent to participate in the study is obtained from the school principals of the three size-matched schools, a member of the research team will randomly assign schools to one of three study arms: (1) You-CAN led by school staff (school-led You-CAN); (2) You-CAN led by school staff and research team (research-led You-CAN); (3) and comparison group (See Fig. 2). The random intervention assignment will be carried out using R software [29].

Both school-led You-CAN and research-led You-CAN will implement the You-CAN intervention, with the key difference being that schools in the research-led arm will participate in monthly video calls with the research team using the video communication platform Zoom [32]. These additional video call touchpoints will result in data collected for Hypothesis 2. The school-led You-CAN arm is the more feasible version of the intervention to be implemented in schools upon study completion. The comparison group will not implement the You-CAN intervention; however, the schools will participate in the school-wide administration of the CRSS-M (see Outcome Measures section below). The comparison group will be invited to deliver You-CAN in the subsequent year, after data collection has been completed. All schools regardless of study arm will receive an honorarium for participating and a summary of the study results.

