#### Concussion awareness campaign

The Concussion Council will run a week-long concussion awareness campaign. Creativity is encouraged and Concussion Councils will implement their own unique ideas that they believe will raise awareness in their school environment. There are no mandatory structured activities that must be done during the concussion awareness campaign. Any information about concussion being shared in the campaign must come from the resources on the *You-CAN Web Portal* that have been reviewed for content accuracy. If a school creates or finds a new resource for their campaign that is not on the *You-CAN Web Portal* then the resource must be approved by the research team prior to inclusion in the concussion awareness campaigns.

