### Data analysis

#### Hypothesis 1

To examine the first research hypothesis, the following analyses will be performed. Data from the CRSS-M will be screened for outliers, and items will be screened for multicollinearity. CRSS-M data will be included for analysis if 90% of questions per section are answered and if there are matching unique identification codes from pretest {T_0_} to posttest {T_1_}. Descriptive statistics will be used to analyze demographics, true/false, checkbox and Likert scales responses. Paired sample t-tests will be used to detect changes in individual responses at pretest {T_0_} and posttest {T_1_} time points. A repeated measure ANOVA will be used to investigate differences in the 3 study arm schools (school-led You-CAN, research-led You-CAN and comparison group) from pretest {T_0_} and posttest {T_1_}. Co-variate adjustments will be completed depending on baseline means. Change scores from each You-CAN study arm will be compared across factors using a multifactorial ANOVA. Post-hoc tests (α = 0.05) will be used to determine the mean differences between each study arm. The school environment survey data will be analyzed through a descriptive univariate analysis. To determine the influence of school factors and additional activities completed by the Concussion Councils on CRSS-M change scores, co-variate adjustments and a multifactorial linear regression will be completed. Statistical analyses will be completed using SPSS [40]. Equivalent non-parametric approaches to analyses will be used should the data not meet necessary assumptions (e.g., normal distribution etc.).

#### Hypothesis 2

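### Schools are randomised, but the Hypothesis 1 tests are student-level with no stated allowance for within-school correlation, so arm comparisons are anti-conservative whenever schools within a board change differently

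*Protocol article*

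**What the plan says.** The Study design section describes the trial so: "This longitudinal study uses a cluster randomized trial design with two intervention groups and an untreated comparison group". Under Intervention assignment, "a member of the research team will randomly assign schools to one of three study arms", so the school is the randomised unit. The abstract gives the numbers: "Three high schools from six randomly selected Canadian school boards will participate and be randomized to three study arms". That makes 18 schools, six per arm, with one school per arm in each board. The School recruitment section adds the matching: "Selected schools will be matched for school size prior to the random allocation to the study arms".

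The Data analysis section, under Hypothesis 1, keeps a survey only if its identification code links the two time points. It then names paired t-tests on individual responses and, for the arms, "A repeated measure ANOVA will be used to investigate differences in the 3 study arm schools". A multifactorial ANOVA of change scores, post-hoc tests at 0.05, a multifactorial linear regression on school factors and additional activities, and non-parametric equivalents follow. It names no school effect, mixed model, generalised estimating equation, cluster-robust standard error, school-level summary or board term. School characteristics appear only as explanatory variables.

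The Sample size section says "The sample size was calculated using an effect size of 0.20 (α = 0.05 and power = 0.80"), expects about 10% attrition and arrives at 140 students per school. It gives no ICC and no design effect.

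**The concern.** The number of independent units for comparing arms is the number of schools. Students in one school share teachers, peers and whatever happens there during the year. Their changes from T0 to T1 can therefore be correlated even if the programme does nothing. Taking the difference between time points removes stable school differences. It does not remove differences in how schools drift.

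A student-level ANOVA treats roughly 2,268 students (18 × 126) as independent, with about 2,265 error degrees of freedom. The randomised-block layout supports about 10 (18 − 1 − 2 for arm − 5 for board). If schools in the same board drift differently, the test takes that drift for an arm difference. What is at stake is the trial's main claim, on which the Discussion section expects school boards to base decisions.

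This is not a detail that an article leaves to an analysis plan. The tests are named for the primary outcome, down to the post-hoc significance level and the software, and as named they do not fit the design.

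**Working it through.** **Inputs from the article.** Six boards × three schools = 18 schools, six per arm. 140 students per school less 10% attrition = 126 analysed, so 6 × 126 = 756 per arm. Effect size 0.20, α 0.05, power 0.80.

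**Assumptions.** The ICC of the change score, the share of school variance lying between boards, and 126 analysed in every school. The article gives none of these directly.

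**The plan's own figure, 140 per school.** The stated inputs do not determine it.
- Two means, d = 0.20, two-sided: 2(1.96 + 0.84)²/0.04 ≈ 393 per arm. 393/0.9 ≈ 437, and 437/6 ≈ 73 per school.
- Repeated-measures ANOVA, three groups, two times, f = 0.20, zero pre-post correlation: 124 in total, rounded to 126. 126/0.9 = 140, but as a total over all arms.
- d = 0.20 with an ICC of about 0.0074: 756/(1 + 125 × 0.0074) ≈ 393 effective per arm. This also matches 126 analysed, or 140 enrolled, per school.

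The choices behind the last two are not stated, so the figure cannot show whether clustering was considered at the design stage.

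**True error of the student-level pairwise test.** Set the total variance of the change score to 1, with ICC ρ and share s of the school variance between boards. Each board supplies one school to each arm, so board variance cancels from the arm difference. The ratio of true to assumed variance is then

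R = (1 − ρ) + 126 ρ (1 − s),

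which is the usual 1 + 125ρ when s = 0. The true two-sided error is 2[1 − Φ(1.96/√R)].

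| ρ | R, s = 0 | error | R, s = 0.5 | error |
|---|---|---|---|---|
| 0.001 | 1.125 | 6.5% | 1.06 | 5.7% |
| 0.005 | 1.625 | 12.4% | 1.31 | 8.7% |
| 0.01 | 2.25 | 19.1% | 1.62 | 12.4% |
| 0.02 | 3.50 | 29.5% | 2.24 | 19.0% |
| 0.05 | 7.25 | 46.7% | 4.10 | 33.3% |

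With s = 1, R = 1 − ρ and the error is 4 to 5%: no inflation.

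**Three-arm test, s = 0.** The error is approximately 0.05^(1/R): 16, 26, 43 and 66% at ρ = 0.005, 0.01, 0.02 and 0.05.

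**Effect of the board term once schools are modelled.** With ρ = 0.02 and half of it between boards, the standard error with board relative to without is √[(0.01 + 0.98/126)/(0.02 + 0.98/126)] = √(0.0178/0.0278) = 0.80. Omitting board costs precision and does not create false positives.

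**Does the alternative hold its level?** In simulated null trials with this layout, a board-blocked analysis of the 18 school means rejected in about 5% of trials.

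**Power with the school as the unit.** For d = 0.20 the non-centrality is 0.20/√(2R/756), with R taken at s = 0 (no credit for matching), on a t distribution with 10 degrees of freedom.
- ρ = 0.01: non-centrality 2.59, power about 65%
- ρ = 0.02: 2.08, about 47%
- ρ = 0.03: 1.78, about 37%
- ρ = 0.05: 1.44, about 26%

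Treating the 756 per arm as independent gives Φ(0.20/√(2/756) − 1.96) = Φ(1.93) ≈ 97%.

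**The case against.** The strongest case on the other side has five parts.

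- **The size is unknown.** The article gives no ICC. The relevant one is that of the change score, which may be lower than that of the raw score. At 0.001 the problem is minor. This stands, and the size must be given as conditional. The figure of 126 is also an assumption: eligible schools can have as few as 100 students, all students are invited, and only linked and nearly complete surveys count.
- **The matching cancels part of it.** This stands too. The s = 0 column is the upper case.
- **The text does not exclude a school term.** The factors of the multifactorial ANOVA are not named, and the regression includes school characteristics. That is correct, but none is stated. School characteristics as covariates do not model the remaining correlation. School as a fixed factor is no remedy either, because arm is constant within school.
- **Campaign freedom does not prove the point.** The article says "There are no mandatory structured activities that must be done during the concussion awareness campaign". A reader might infer that this builds in the inflation. If the programme has no effect anywhere, differing campaigns create no variation in change, and comparison schools run none. The argument for false positives rests on ordinary drift between schools. Varied campaigns matter for precision when the programme does work.
- **The errors are two-sided.** For a single pairwise comparison, about half of the false positives would go against the programme. The percentages are not rates of wrongly declaring benefit.

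The core remains: schools are allocated, students are tested, and no link between the two is stated.

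**Conclusion.** The point holds and should be fixed before analysis. The named tests understate the standard error of every arm comparison unless schools within a board all change alike. If the change-score ICC is 0.01 to 0.05, a nominal 5% pairwise test has a true error of about 19 to 47% with all school variance within boards, and about 12 to 33% with half of it between boards. Near 0.001 the excess is only one or two points.

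Three stronger readings are tempting and not supported:
- A reader might infer that ignoring the board triplets also makes p-values too small. It works the other way: leaving out a stratum balanced across arms tends to make a test conservative.
- A reader might infer that severe inflation is established. It depends on an ICC, a board share and a cluster size that the article does not give.
- A reader might infer that the sample size ignored clustering. 140 per school is compatible with an unstated ICC of about 0.0074, so the article does not settle this.

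The Hypothesis 1 text mentions no confidence intervals. Any computed from these models would be too narrow for the same reason.

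**What to change.** For the arm comparisons, replace the student-level t-tests and ANOVAs with one linear mixed model for the T1 score. Take arm, baseline score and board (the size-matched triplet) as fixed effects and school as a random effect, with Kenward-Roger or Satterthwaite degrees of freedom (about 10). A simpler alternative is a board-blocked ANOVA of the 18 school-level adjusted means. The two need not agree exactly when school numbers differ, so name one as primary. As the distribution-free fallback, use a permutation test of arm labels within boards in place of rank tests on students.

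Keep the regression on school factors and additional activities, since it answers a separate question, but fit it with a school random effect or at school level.

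The change needs no new data. Its cost is wider intervals and a lower honest power. For d = 0.20 the power falls to about 65, 47, 37 or 26% at an ICC of 0.01, 0.02, 0.03 or 0.05 before any gain from matching. The 80% in the Sample size section should therefore be restated with the effect-size metric and an explicit ICC.

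### Baseline adjustment depends on the observed baseline means, with no stated trigger, and the arm comparisons otherwise reduce to unadjusted change scores

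*Protocol article*

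**What the plan says.** All of this stands in the protocol article, Data analysis, Hypothesis 1.

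- Arm comparison: "A repeated measure ANOVA will be used to investigate differences in the 3 study arm schools", from T0 to T1.
- Adjustment, in the next sentence: "Co-variate adjustments will be completed depending on baseline means". No trigger is given, and the T0 score is not named as a covariate.
- Then: "Change scores from each You-CAN study arm will be compared across factors using a multifactorial ANOVA".
- Later, to study school factors and the councils' additional activities: "on CRSS-M change scores, co-variate adjustments and a multifactorial linear regression will be completed". The T0 score is not named here either.

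Only records with matching T0 and T1 codes enter the analysis, so every analysed student should have a T0 record. On design, the Abstract (Methods) says "Three high schools from six randomly selected Canadian school boards will participate and be randomized to three study arms". That is 18 schools, 6 per arm, each board supplying one size-matched triplet.

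**The concern.** A rule that decides on adjustment after the baseline means are seen has three weaknesses.

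1. A gap judged too small to act on stays in the estimate. Regression to the mean then carries part of it into the change-score contrast.
2. With no trigger written down, the adjusted and unadjusted results are both available and nothing says which one counts. The Goals section lists six constructs, so the choice could fall differently from scale to scale.
3. When T0 is not used as a covariate, precision is usually lost.

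Table 2 places T0 in October 2019 and T1 in May 2020, and the article appeared in February 2020. Baseline means could therefore be available before any trigger is fixed.

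**Working it through.** **The plan's own figure.** The Sample size section states effect size 0.20, α = 0.05, power 0.80 and about 10% attrition, and concludes "we require 140 participants to complete the survey at each participating high school". Two independent means at d = 0.20, two-sided, need 393 per arm; 393/0.90 = 437; 437/6 = 73 per school. So 140 is not reproduced from the printed inputs. Keeping 90% of 140 leaves 126 per school and 126 × 6 = 756 per arm. Then 756/393 = 1.92, which would be a design effect at ICC 0.92/125 ≈ 0.007. An unstated ICC could thus explain 140, and I do not call it wrong. Below I use only m = 126 students per school and 6 schools per arm.

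**What the unadjusted analysis is.** With T0 and T1 only, the arm-by-time F test equals the one-way ANOVA F test on T1 − T0.

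**Student level, independence assumed.** In units of 2σ²/n, the variance of the arm contrast is 2(1−r) for change scores and 1−r² with T0 as covariate. The ratio is (1+r)/2.

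| r (assumed) | variance ratio | extra n for change scores |
|---|---|---|
| 0.3 | 0.65 | 54% |
| 0.5 | 0.75 | 33% |
| 0.7 | 0.85 | 18% |

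**Conditional rule, simulated.** The trigger (baseline p < 0.05) is my assumption. Units were either 393 independent students per arm or 6 school means per arm, with r = 0.3, 0.5 and 0.7.

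- Average bias with 393 students per arm: about 0.001 SD or less, within simulation error.
- Type I error when the rule is followed mechanically: 0.034 to 0.048.
- Type I error when either result may be reported: 0.066 to 0.079.
- Power at d = 0.20 with 393 students per arm, rule versus always adjusting: 0.67 vs 0.83, 0.81 vs 0.89, 0.95 vs 0.97.
- SD of the estimate with 6 school means per arm, rule versus always adjusting: 0.667 vs 0.590, 0.572 vs 0.533, 0.445 vs 0.436.

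**Cluster design.** Assume total SD 1, within-school r = 0.5, ICC ρ, and school-level T0–T1 correlation R. For school means, V = ρ + (1−ρ)/126, C = ρR + 0.5(1−ρ)/126 and c = C/V.

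- SE of the baseline gap between two arms: √(2V/6), ignoring any gain from matching.
- Change-score bias given a gap D: −(1−c)D.
- Variance per school mean: 2(V−C) for change scores; V − 2(0.5)C + 0.25V with student T0 only; V(1−c²) with school-mean T0 as well.

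| ICC | R | c | SE of gap | change-score bias at a one-SE gap (share of 0.20) | SE ratio to change: student T0 only | SE ratio: plus school-mean T0 |
|---|---|---|---|---|---|---|
| 0.007 | 0.5 | 0.50 | 0.070 | 0.035 (18%) | 0.87 | 0.87 |
| 0.02 | 0.5 | 0.50 | 0.096 | 0.048 (24%) | 0.87 | 0.87 |
| 0.02 | 0.8 | 0.72 | 0.096 | 0.027 (14%) | 0.97 | 0.93 |
| 0.02 | 0.95 | 0.82 | 0.096 | 0.017 (8%) | 1.10 | 0.95 |
| 0.05 | 0.8 | 0.76 | 0.138 | 0.033 (17%) | 1.01 | 0.94 |

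Worked row, ICC 0.02 and R 0.95: V = 0.02 + 0.98/126 = 0.02778 and C = 0.019 + 0.00389 = 0.02289. Change scores give 2(V−C) = 0.00978; student T0 only gives 0.01183; √(0.01183/0.00978) = 1.10.

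The last column treats the school-level slope as known. With 18 − 1 − 2 − 5 = 10 residual degrees of freedom for arm and board, estimating it multiplies the variance by about 1 + 1/(10−2) = 1.125, so the SE by 1.06. The last column then runs from about 0.92 to 1.01.

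**The case against.** The strongest reply is that schools are randomised, so change scores, baseline adjustment and a symmetric rule choosing between them are all unbiased over allocations. That stands. A reader might infer that the rule biases the treatment effect, and the documents do not support that. Followed mechanically under the assumed trigger, the rule was even conservative.

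A second reply is that student-level variance ratios do not carry over to a trial that randomises schools. That also stands. If school means are very stable, adjusting for the student's T0 score alone can be less precise than change scores (SE ratio 1.10 at ICC 0.02, R 0.95). Given a baseline gap, it also leaves its own bias of (c − 0.5)D, here 0.32D against −0.18D for change scores. A reader might infer that adjustment always gains precision at no cost; that is not established.

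Third, a trigger and covariate list are commonly left to an analysis plan that is not shown. That is fair, and their absence alone would be no finding. But the article does state a rule, and that rule makes adjustment turn on the data. A fuller trigger would limit the discretion but not the conditional bias.

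Fourth, the change-score ANOVA across factors need not be the main arm contrast, the later regression does include covariates, and size-matching within board may limit imbalance. These points soften the concern. None fixes adjustment for T0 in any arm comparison. Nor does the article show that anyone chose an analysis after seeing the baseline data; the dates show only that this was possible.

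**Conclusion.** The point holds in a limited form and should be acted on. The stated rule makes adjustment data-dependent, and the named arm comparisons fall back on unadjusted change scores when it is not triggered. That fallback is my reading of the models, since the article does not say it in words.

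The harm is bias conditional on the observed imbalance, not average bias. At an ordinary one-SE baseline gap it is about 8% to 24% of the 0.20 target in the scenarios tabulated. Added to this are a type I error of about 0.07 to 0.08 if the choice between results is free, and usually some loss of precision. The precision figure is a range: student-level variance ratios of 0.65 to 0.85, shrinking or reversing at cluster level according to the ICC and R. All sizes rest on assumed r, R and ICC, none of which the article gives; the simulated error rates also rest on the assumed p < 0.05 trigger. The case for the change rests mainly on removing discretion and conditional bias, with precision second.

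**What to change.** Replace the sentence on covariate adjustment with:

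*Every arm comparison will be adjusted for the student's T0 score on the same scale, the school-mean T0 score, and board (the size-matched triplet), regardless of observed baseline differences, with T1 as the outcome in a model that accounts for school.*

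Make the unadjusted change-score ANOVA supportive only. The school-mean term is needed because student-level adjustment alone can do worse than change scores when school means are stable.

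The cost is one between-school degree of freedom (10 to 9 by the count above), with the variance cost of estimating its slope already shown, and a model that accounts for school in place of the plain repeated measures ANOVA. The T0 scores and board membership are already collected.

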#### You-CAN web portal

The *You-CAN Web Portal* has been developed by the research team, and contains evidence-based concussion resources [37], as well as instructions and timelines for the Concussion Council. Each participating school will have a unique login for the *You-CAN Web Portal*, allowing each Concussion Council to upload documents to their account. The *You-CAN Web Portal* will also be used as a method of communication with the research team and include functionalities such as email and video-calling. The *You-CAN Web Portal* will also contain an instructional handbook for school staff participants.

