### Secondary outcome measures

The secondary outcome of the study is to understand the implementation fidelity, acceptability, and student and school staff experiences with the You-CAN intervention using the outcome measures described below.

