#### You-CAN web portal analytics

Google Analytics [39] data for the *You-CAN Web Portal* domain will be downloaded on a monthly basis throughout the duration of study. This will provide data on number of users, average time on pages, location of users, operating system and devices used to access the web portal, bounce rates, behaviour flow, in-page analytics, traffic sources, form abandonment, form submissions, and how often pages were printed.

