To examine the second research hypothesis (H_2_), the following analyses will be performed. A descriptive univariate analysis of web portal analytic data will be completed, and compared across time. Research field notes from monthly video calls will be analyzed using categorical descriptive statistics, and content of open-ended questions will be coded and counts will be reported across coded domains. Campaign details surveys will be analyzed using descriptive statistics and frequencies. Open-ended responses will be coded and coded domains will be reported as counts (frequencies and percentages). All items created by Concussion Councils (resources, showcase presentations) will be analyzed using a content analysis [41]. This includes identifying patterns across information and visual mediums in a replicable and systematic manner, and has been used to evaluate concussion resources [42, 43]. A customized coding scheme will be developed by randomly selecting a small number of resources to be assessed prior to data analysis in order to develop and refine the coding scheme (e.g. type of image, primary content of image, purpose of image, information quality). Post-showcase survey Likert scale questions will be reported as frequencies and percentages. Open-ended questions will be coded and categorized and codes will be reported as frequencies. All exit interviews with student and school staff participants will be analyzed using a deductive thematic analysis [44]. Two independent researchers will review transcripts and generate codes across all interviews. To ensure rigour, a third member of the research team will consult at each stage of the comparative analysis to ensure the codes and themes are representative of the data. Through these analyses, information will be provided about the acceptability of the You-CAN intervention.

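### Web-portal use is planned as a domain-level monthly series compared across time, so it would not show use by council or by You-CAN arm, although each school has its own login (minor)

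*Protocol article*

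**What the plan says.** Secondary outcome measures opens with the purpose: "The secondary outcome of the study is to understand the implementation fidelity, acceptability, and student and school staff experiences". The measures that follow serve that purpose, and portal analytics is the first of them.

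You-CAN web portal analytics fixes the level and frequency of collection: "data for the *You-CAN Web Portal* domain will be downloaded on a monthly basis throughout the duration of study". It then lists the metrics: "This will provide data on number of users, average time on pages, location of users, operating system and devices used to access the web portal", followed by bounce rates, form submissions, printing and similar items. School, login and study arm are not in the list.

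Data analysis, Hypothesis 2, gives the analysis: "A descriptive univariate analysis of web portal analytic data will be completed, and compared across time".

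You-CAN web portal, under Delivery, says: "Each participating school will have a unique login for the *You-CAN Web Portal*, allowing each Concussion Council to upload documents to their account". The same section makes the portal a channel for contact between councils and the research team.

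**The concern.** The unit in which portal use is described is not the unit that was randomised. Schools were allocated to arms and each You-CAN school runs its own council, so fidelity is a property of a school. A total for the domain can look healthy because a few councils use the portal heavily while others do not use it at all.

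Portal use is also closer to fidelity here than in many programmes. The campaign has no compulsory activities, but the information shared must come from portal resources or be approved by the research team. The portal also holds the council's instructions and timelines and the staff handbook. Whether a council opened it is therefore a useful adherence check.

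The contrast between the two You-CAN arms adds to this. They differ mainly in the monthly video contact with the researchers, and Intervention assignment describes the school-led arm as the more feasible one to run after the study. Whether school-led councils keep using the portal without that contact is a natural question, and a pooled series would not answer it.

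**Working it through.** No sample-size, power or alpha figure bears on this point, and the plan states no figure for portal use that could be reproduced. The check is a count of units and a comparison of sections.

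**Inputs**
- Boards: 6, each supplying 3 size-matched schools, one to each arm (Abstract, Methods; School recruitment; Intervention assignment).
- Arms that deliver You-CAN: 2 of 3 (Intervention assignment).
- Months of portal analytics: October to May, which is 8 (Table 2).
- Login unit: the school (You-CAN web portal).

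**Counts**
- You-CAN schools: 6 boards × 2 arms = 12.
- Values per metric as written: 1 domain × 8 months = 8.
- Values per metric by arm: 2 arms × 8 months = 16.
- Values per metric by school: 12 schools × 8 months = 96.

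The count of 12 assumes full recruitment and that only schools with a council use the portal.

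**Sections side by side**
1. Collection is at domain level and the listed metrics carry no school or arm field. The analysis names time as its comparison. For Hypothesis 1, by contrast, the same Data analysis section names comparisons between arms explicitly.
2. User location is collected, but it cannot be relied on to recover the arm. Each board places one school in each arm, so a location that identifies the board still covers a school-led and a research-led school. The article does not give the geographic resolution.
3. The key that does identify the school, and through it the arm, already exists: "Each participating school will have a unique login for the" portal, "allowing each Concussion Council to upload documents to their account". The portal-analytics and Hypothesis 2 sections do not say that it will be used to break down the traffic.
4. Because the login belongs to the school, a number of users taken from the analytics should not be read as a number of council members.
5. The research team communicates through the portal. The article has no rule that includes or excludes its visits. It gives neither the number of team users nor how often they visit, so the effect on the totals cannot be sized.
6. Table 2 schedules two other sources monthly or nearly so. Field notes run from October to May but only in the research-led arm. Created content is collected from January to April. Portal analytics is thus the only measure in the table collected every month from October to May in both You-CAN arms.

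**The case against.** The strongest reply is that this is a condensed article and the point reads silence as a decision. Nothing says that the arms will be pooled, that the logins will be ignored or that other breakdowns are ruled out. Subgroup summaries and filters for internal traffic are often left to a fuller document. The protocol promises no by-arm fidelity result from the analytics: the Hypothesis 2 section ends by saying that its analyses inform acceptability, and the Discussion looks to the qualitative data for both acceptability and fidelity. Council-level evidence also exists in both You-CAN arms, from the campaign details survey, created content and showcase slides, the additional-activities sheet and the exit interviews. These would help to expose an inactive council.

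Much of this stands. It limits the point to the method as stated and keeps it minor. A reader might infer that school-level use can never be recovered. The documents do not support that, since logins and council accounts exist. A reader might also infer that research-team traffic is counted as use. That too is unsupported, because the text is silent either way, and the team's approval and review of resources is not said to take place on the portal.

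What remains is not mere silence. The article does state a level of collection (the domain) and a comparison (time), and these do not identify the randomised unit. The other sources are mostly one-off or reported by the councils, so they complement a monthly record of use but do not replace it.

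**Conclusion.** The point holds as a minor improvement to one descriptive secondary measure. Followed as written, the plan gives 8 monthly values per metric for the domain, where the existing logins could support up to 96 school-months. Those 8 values would not show councils without any use, or a difference in use between the school-led and research-led arms.

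This rests on taking the stated collection level and comparison at face value, and on 12 You-CAN schools being recruited. It does not show that fidelity cannot be assessed in this trial, and no bias from team visits is established. The primary outcome, the sample size and the Hypothesis 1 analysis are untouched.

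**What to change.** In You-CAN web portal analytics, state that use will be captured per school login and month. In Data analysis, Hypothesis 2, state that:
- portal use (for example sessions, page views, resources opened and forms submitted) will be derived per school login per month;
- the number of councils with any use will be reported for each month;
- use will be summarised descriptively by You-CAN arm, with schools grouped by board, as well as over time;
- any research-team visits will be excluded;
- counts of users will not be interpreted as counts of council members, because the login is held by the school.

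No test between arms is needed. The cost is a small set-up effort to tag the logins in the analytics or to use portal login records, with no new participants or instruments. It is best done before data capture starts, since totals that were not tagged may be impossible to split afterwards. If capture has already begun, login records and the uploads in each council's account are the place to look.
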